### Participants

#### Eligibility criteria

Male individuals of legal age diagnosed with locally advanced or metastatic prostate cancer and undergoing androgen deprivation therapy (ADT) are eligible for inclusion in this randomized controlled trial. The primary objective was to assess the impact of a structured physical exercise intervention on physical function, cancer-related fatigue, and quality of life in this patient population. Participants are randomly allocated to one of two groups: those in the intervention arm received supervised exercise in accordance with the SPoRT-PCa-ADT Program, while those in the control arm are provided with a home-based exercise regimen following an initial evaluation, supported by weekly telephone follow-ups.

The inclusion and exclusion criteria are presented in the Table 1, following the recommendations of previous randomized controlled trials to target an clinically homogeneous population, maximizing potential benefits and be consistent with exercise guidelines for cancer patients [8, 22].

**Table 1 Tab1:** Inclusion and exclusion criteria

Inclusion criteria	Male participants aged 18–80 years Diagnosis of locally advanced or metastatic prostate cancer Currently receiving androgen deprivation therapy (ADT) Treatment at Urology and oncology departments within the University Clinical Hospital “Virgen de la Arrixaca” healthcare network Legal capacity and signed informed consent Ability to attend supervised sessions or perform home-based exercises safely Physician clearance for exercise participation
*Exclusion criteria*	Unwillingness to participate in the study Inability to complete adequate follow-up Uncontrolled or symptomatic metastatic bone disease Physical disabilities that would prevent participants from safely completing the protocol Severe cardiovascular disease or contraindications to exercise determined by assessment Participation in structured resistance training within the previous 6 months Cognitive impairment limiting ability to follow exercise instructions Uncontrolled hypertension (> 160/100 mmHg) Active treatment for other primary cancers

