#### Blinding

Due to the nature of the exercise intervention, blinding of participants and exercise physiologists is not feasible, which is consistent with the inherent limitations of behavioral intervention trials [30]. However, outcome assessors for objective physical measures remain blinded to group allocation where possible to minimize detection bias. All patient-reported outcome measures are self-administered electronically to eliminate potential assessor influence. Data files are anonymized using coded identifiers by an independent researcher prior to processing by study personnel, and data analysis will be conducted by statisticians blinded to group allocation [31]. To minimize performance bias, participants are informed that there is equal possibility of assignment to either treatment group, and that the relative effectiveness of two different exercise interventions is under investigation, without suggesting superiority of either approach.

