### Assessment protocol

All participants undergo identical assessment procedures irrespective of group allocation. Baseline assessments are conducted within two weeks prior to randomization, and post-intervention assessments are scheduled within two weeks following completion of the 24-week intervention period. Midpoint assessments of patient-reported outcomes are conducted at week 12 and are administered either at the training center or during specialized urological consultations as part of routine oncological follow-up. To reduce the influence of diurnal variation, all physical performance assessments are scheduled at the same time of day for each participant (± 1 h). Participants are instructed to refrain from strenuous physical activity for 48 h prior to testing, maintain adequate hydration, and abstain from caffeine and alcohol for 24 h before each assessment (Fig. 2).

Physical assessments are conducted by qualified sports scientists with training in exercise oncology. Due to logistical constraints, assessors are not blinded to group allocation. However, patient-reported outcomes are collected using standardized, self-administered questionnaires to mitigate potential assessor bias. Venous blood samples are drawn by certified phlebotomists and analyzed by laboratory technicians blinded to group assignment. To ensure procedural consistency, comprehensive standard operating procedures (SOPs) are developed prior to study initiation, and all research personnel complete structured training. Ongoing quality control procedures are implemented throughout the study to uphold methodological rigor.

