### Program monitoring and safety

The incidence and severity of adverse events during exercise sessions are systematically monitored and reported by supervising exercise physiologists using standardized documentation. Events are classified by type and severity, with participants also self-reporting any adverse events between sessions. A Data Safety Monitoring Board reviews all events to ensure participant safety, with serious adverse events are reported to the institutional Ethics Committee immediately upon identification and formally documented within 24 h.

Exercise adherence (percentage of scheduled sessions attended) and protocol compliance (actual loads, repetitions, and velocity parameters) are tracked to calculate total training volume and intensity received by each participant. Program adherence of ≥ 85% is required for per-protocol analysis, with strategies to maximize adherence including follow-up calls, flexible scheduling, and transportation assistance when feasible. Participants can withdraw at any time without prejudice to their ongoing care, and investigators can withdraw participants if they meet exclusion criteria or if continued participation is deemed potentially harmful.

No formal interim efficacy analyses are planned for this trial. Given the nature of the intervention and the study population, no independent Data Safety Monitoring Board (DSMB) has been constituted. Safety monitoring will be conducted by the principal investigator and the supervising exercise physiologists throughout the 24-week intervention period. Early termination of the trial may be decided by the principal investigator in consultation with the Clinical Research Ethics Committee of the University Clinical Hospital ‘Virgen de la Arrixaca’ if: (i) there is clear evidence of harm attributable to either intervention; (ii) enrolment falls below 50% of the target sample after 12 months of active recruitment; or (iii) continued participation is deemed clinically unjustifiable. All decisions regarding early stopping and their rationale will be formally documented.

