### Statistical analyses

Statistical analyses will be performed using JAMOVI (version 2.5, The JAMOVI Project, Sydney, Australia). Descriptive statistics will be calculated for all variables, with data presented as means and standard deviations for continuous variables and frequencies and percentages for categorical variables. Graphical representations will be generated using GraphPad Prism (version 10, GraphPad Software Inc., San Diego, CA, USA).

The primary analysis will include all participants who completed both baseline and post-intervention assessments in their respective groups. Additional sensitivity analyses will be conducted using intention-to-treat principles, with missing data handled using multiple imputation by chained equations (MICE) with predictive mean matching for continuous variables. For all outcome measures, analysis of covariance (ANCOVA) will be used to compare post-intervention values between groups while adjusting for baseline values and stratification variables (age group and ADT duration).

Bonferroni post-hoc corrections will be applied for multiple comparisons across outcome measures. Effect sizes will be calculated using Cohen’s d for between-group differences and partial eta-squared for ANCOVA models, with values of 0.2, 0.5, and 0.8 considered small, medium, and large effects for Cohen’s d, respectively [45]. For all analyses, *p* < 0.05 will be considered statistically significant. Per-protocol analyses will be conducted as sensitivity analyses, including only participants with ≥ 85% adherence. Exploratory subgroup analyses will examine potential effect modification by baseline characteristics including age, ADT duration, and baseline functional status. Correlation analyses will examine relationships between changes in objective physical performance measures and patient-reported outcomes within each group.

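### Investigator withdrawal is not separated from the end of follow-up, so men withdrawn for worsening health can drop out of the completer primary analysis

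*Protocol article*

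**What the plan says.** Program monitoring and safety gives the withdrawal rule: "investigators can withdraw participants if they meet exclusion criteria or if continued participation is deemed potentially harmful". The same section says that "Safety monitoring will be conducted by the principal investigator and the supervising exercise physiologists". It states both that a safety board reviews all events and that no independent board has been constituted, so independent review of these decisions is not assured.

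Several exclusion criteria in Table 1 (Eligibility criteria) can arise after randomisation and mark deterioration. One is "Uncontrolled or symptomatic metastatic bone disease"; others concern severe cardiovascular disease, cognitive impairment and physical disability. Being unable to complete follow-up is also on the list.

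Statistical analyses sets the primary population: "The primary analysis will include all participants who completed both baseline and post-intervention assessments in their respective groups". The analysis that keeps everyone comes second: "Additional sensitivity analyses will be conducted using intention-to-treat principles, with missing data handled using multiple imputation by chained equations (MICE" is how that sentence begins.

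On blinding, the Blinding section says that "blinding of participants and exercise physiologists is not feasible". It has physical outcome assessors blinded where possible, whereas Assessment protocol says: "Due to logistical constraints, assessors are not blinded to group allocation".

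No section says that a withdrawn man is still assessed at week 24.

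**The concern.** Each clause is ordinary by itself. A safety withdrawal clause is normal practice, and the clinical criteria are not questioned here. The difficulty lies in the combination. The rule refers to withdrawing participants, not to stopping the exercise, and the primary analysis then conditions on having a post-intervention assessment. Men taken out because their disease or general health got worse are likely to be men with poor week-24 outcomes, and adjusting for baseline does not recover a decline that happens after baseline.

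Losing such men biases the comparison if it happens at different rates in the two arms. The protocol gives reasons to think it might. Supervised men have side effects and readiness checked at each of 48 sessions, while controls are followed by a weekly telephone call. The exercise physiologists, who know the allocation, share the safety monitoring. At stake is whether the primary result compares the groups as randomised.

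**Working it through.** **Plan's own figures.** Inputs from Sample size: f = 0.25 (from d = 0.5), alpha 0.05, power 0.95, 2 groups, 3 measurements, correlation 0.5, 15% dropout.

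- Noncentrality = f² × N × m / (1 − ρ) = 0.0625 × 44 × 3 / 0.5 = 16.5, with 2 and 84 degrees of freedom. Power is 0.956 at N = 44 and 0.946 at N = 42, so 44 reproduces.
- 44 / 0.85 = 51.8, rounded up to 52 (26 per arm). This also reproduces.
- The plan therefore expects about 52 − 44 = 8 men, or 4 per arm, to be missing for any reason.

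**Net shift from selective withdrawal.** If k of 26 men in an arm are withdrawn and their week-24 mean would have been w SD worse than that of the rest, the completer mean exceeds the full-arm mean by (k/26) × w. The shift in the group difference is

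shift = w × (k_supervised − k_control) / 26.

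The values of k and w are assumptions; the documents give neither. With w = 1:

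| Withdrawn, supervised vs control | Net shift (SD) | Share of 0.5 SD |
|---|---|---|
| 2 vs 2, or 4 vs 4 | 0 | 0% |
| 3 vs 2 | 1/26 = 0.038 | 8% |
| 2 vs 0, or 4 vs 2 | 2/26 = 0.077 | 15% |
| 4 vs 0 | 4/26 = 0.154 | 31% |

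The 4 versus 0 row uses up the whole 15% dropout allowance of one arm (4/26 = 15.4%), so it is an upper case. Varying w from 0.5 to 1.5 takes the two rows with no control withdrawals from 2/26 × 0.5 = 0.04 SD to 4/26 × 1.5 = 0.23 SD. If more controls were withdrawn, the sign would reverse.

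**Check under the planned type of model.** A simulation used 26 men per arm, true effect 0, ANCOVA adjusted for baseline, correlation 0.5, and 5,000 runs per scenario:

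| Withdrawal, supervised vs control | Shift (SD) | Rejection at 5% |
|---|---|---|
| None | 0.00 | 4.7% |
| 4 at random vs 0 | 0.00 | 5.2% |
| Worst 1 vs 0 | 0.06 | 6.9% |
| Worst 2 vs 0 | 0.11 | 8.6% |
| Worst 4 vs 0 | 0.21 | 15.0% |
| 4 vs 0, withdrawal correlated 0.5 with outcome | 0.10 | 6.8% |
| Worst 4 vs worst 4 | 0.00 | 8.4% |

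Removing exactly the worst men is an extreme form of selection; the row with correlation 0.5 is a milder one. Equal selective withdrawal leaves the estimate unshifted. Its rejection rate is still above 5% because cutting off the poor tail makes the residual variance too small.

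**The case against.** Four points weigh on the other side.

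- **Imputation is planned.** The intention-to-treat analysis would bring withdrawn men back in, and Concomitant care adds that treatment changes will be considered in sensitivity analyses. This stands as mitigation. It does not settle the matter, because the primary result remains the completer one, and withdrawal because of worsening health can breach missing-at-random.
- **Loss of the week-24 visit is an inference.** Nothing expressly cancels assessment after withdrawal, and a full protocol that is not shown might keep these men in follow-up. This stands in part, and the point is therefore conditional on a man having no week-24 assessment. The article does, however, state both the withdrawal rule and the completer population, and it is their combination that is at issue.
- **Differential withdrawal is not demonstrated.** Supervised men also have their loads adjusted for side effects, which could retain men who are deteriorating. The readiness check lists fatigue, resting heart rate and squat velocity but not blood pressure, so closer contact would not obviously detect uncontrolled hypertension. That the principal investigator knows the allocation is also an inference. All this stands, and neither the existence nor the direction of a bias can be asserted.
- **A broader reading of the clause fails.** A reader might infer that it already reaches every supervised man, since Table 1 excludes "Participation in structured resistance training within the previous 6 months". The documents do not support that. The item is an entry criterion about training before the trial, and Concomitant care separates trial training from outside programmes. Read that literally, it would also reach the controls, who have a structured resistance programme of their own, so it would say nothing about selection by arm.

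**Conclusion.** The point holds as a weakness of the plan as written: a man withdrawn by an investigator for worsening health, with no week-24 assessment, is excluded from the primary analysis, and nothing in the article keeps him in follow-up. With a 1 SD worse outcome in withdrawn men, the net shift runs from 0 to 0.15 SD, or 0 to 31% of the planned 0.5 SD, depending on how unequal the withdrawals are. The numbers withdrawn, the 1 SD and the inequality between arms are all assumptions. It would be tempting to conclude that the supervised arm will be favoured. The documents make unequal withdrawal plausible but do not show it, and equal withdrawal gives no shift. The change is worth making because it is cheap and up to about 8 of 52 men are expected to be missing for all reasons together.

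**What to change.** Leave the clinical criteria for stopping exercise as they are, and change the following:

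1. In Program monitoring and safety, state that stopping the exercise programme does not end study participation. Week-12 and week-24 questionnaires, and those week-24 tests the man is cleared for, are still sought unless he withdraws consent.
2. State that he is analysed in his randomised arm.
3. In Statistical analyses, make the analysis of all randomised men primary and the completer analysis a sensitivity analysis. The imputation already planned can serve for what remains missing. Step 1 is needed as well, since changing the analysis set alone supplies no week-24 data.
4. Record, by arm, the reason for each withdrawal and the role that decided it, so that readers can see whether withdrawals differed.

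The cost is protocol wording and a few extra follow-up contacts. Questionnaires are already self-administered electronically, so men who stop exercising can still be reached. The drawback is that some physical tests will remain missing in men not cleared for them, and for those the missing-data assumption still matters.

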### Statistical analyses

Statistical analyses will be performed using JAMOVI (version 2.5, The JAMOVI Project, Sydney, Australia). Descriptive statistics will be calculated for all variables, with data presented as means and standard deviations for continuous variables and frequencies and percentages for categorical variables. Graphical representations will be generated using GraphPad Prism (version 10, GraphPad Software Inc., San Diego, CA, USA).

The primary analysis will include all participants who completed both baseline and post-intervention assessments in their respective groups. Additional sensitivity analyses will be conducted using intention-to-treat principles, with missing data handled using multiple imputation by chained equations (MICE) with predictive mean matching for continuous variables. For all outcome measures, analysis of covariance (ANCOVA) will be used to compare post-intervention values between groups while adjusting for baseline values and stratification variables (age group and ADT duration).

Bonferroni post-hoc corrections will be applied for multiple comparisons across outcome measures. Effect sizes will be calculated using Cohen’s d for between-group differences and partial eta-squared for ANCOVA models, with values of 0.2, 0.5, and 0.8 considered small, medium, and large effects for Cohen’s d, respectively [45]. For all analyses, *p* < 0.05 will be considered statistically significant. Per-protocol analyses will be conducted as sensitivity analyses, including only participants with ≥ 85% adherence. Exploratory subgroup analyses will examine potential effect modification by baseline characteristics including age, ADT duration, and baseline functional status. Correlation analyses will examine relationships between changes in objective physical performance measures and patient-reported outcomes within each group.

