#### Sample size

Sample size calculations are performed using G*Power 3.1.9.7 software [23]. For the primary analysis examining the time × treatment interaction effect, an F-test for ANOVA: repeated measures, within-between interaction is selected. Parameters are set as follows: effect size f = 0.25 (converted from Cohen’s d = 0.5), α error probability = 0.05, power (1-β error probability) = 0.95, number of groups = 2, number of measurements = 3 (baseline, midpoint, post-intervention), correlation among repeated measures = 0.5 (estimated from previous resistance training studies in cancer populations), and nonsphericity correction ε = 1. The moderate effect size (Cohen’s d = 0.5) is selected based on previous research demonstrating moderate to large effects of resistance training interventions on muscle strength and functional outcomes in ADT patients [24, 25]. This analysis determines that 44 participants (22 per group) provide adequate statistical power to detect the hypothesized interaction effect for the primary outcome measures. Accounting for an anticipated 15% dropout rate, based on previous reports from supervised exercise interventions in cancer survivors, 52 participants are targeted for recruitment (26 per group randomized to either the supervised velocity-based training program or the home-based control intervention).

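### The primary analysis is confined to men who complete the week-24 assessment and intention-to-treat is only a sensitivity analysis, so the main result is open to bias, in either direction, from unequal dropout

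*Protocol article*

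**What the plan says.** Statistical analyses in the protocol article fixes the primary population: "The primary analysis will include all participants who completed both baseline and post-intervention assessments in their respective groups". The next sentence gives intention-to-treat its place: "Additional sensitivity analyses will be conducted using intention-to-treat principles", with missing values handled by multiple imputation by chained equations (MICE). A per-protocol analysis is a further sensitivity analysis. The model is the same throughout: "analysis of covariance (ANCOVA) will be used to compare post-intervention values between groups while adjusting for baseline values and stratification variables". No other section makes the as-randomised set primary or gives a reason for choosing completers.

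Sample size plans for a single dropout rate: "Accounting for an anticipated 15% dropout rate, based on previous reports from supervised exercise interventions in cancer survivors, 52 participants are targeted for recruitment". Program monitoring and safety allows removal after randomisation: "investigators can withdraw participants if they meet exclusion criteria", or where continuing is judged potentially harmful.

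**The concern.** Attending week-24 testing happens after randomisation and may depend on the allocated programme. The intervention arm is asked to attend 48 supervised sessions; the control arm trains at home and receives a weekly call. Participants know their allocation. Side effects are reviewed at every supervised session, so problems may also come to notice at different rates in the two arms. Some exclusion criteria, such as symptomatic bone disease or uncontrolled hypertension, can arise during follow-up.

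If the men missing at week 24 differ in outcome from those who stay, and the arms lose different proportions, the completer comparison no longer compares the groups formed by randomisation. Adjusting for baseline and the stratification factors repairs this only as far as those variables explain the loss. The choice applies to every outcome, because the primary set is defined once for the whole trial.

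**Working it through.** **Inputs from the article.** Effect size f = 0.25 (d = 0.5), α = 0.05, power 0.95, 2 groups, 3 measurements, correlation 0.5, ε = 1, 44 evaluable, 15% dropout, 52 recruited (Sample size). ANCOVA on week-24 values adjusted for baseline (Statistical analyses). The article gives no dropout rate by arm and no link between dropout and outcome, so those below are assumptions shown as a range.

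**The plan's own figures reproduce.** For the repeated-measures interaction, λ = f²·N·m/(1−ρ) = 0.0625 × 44 × 3/0.5 = 16.5, with df 2 and 84. Power is 0.956 at N = 44 and 0.946 at N = 42, so 44 is the smallest even N. Dropout: 44/0.85 = 51.8, so 52. These are not in dispute.

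**Men left out.** 52 × 0.15 = 7.8, about 8; expected completers are 52 × 0.85 = 44.2.

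**Bias when the true effect is zero.** Large-sample simulation, outcome SD 1, higher values better, baseline to week-24 correlation 0.5. Dropout is logistic in the week-24 outcome, with log-odds rising by 1 or 2 per SD of worse outcome (odds ratios 2.7 and 7.4). Entries are supervised minus control, in SD, for slope 1 / slope 2. A single normal-model imputation stands in for MICE. Week 12 is assumed to correlate 0.5 with baseline, and 0.5 or 0.7 with week 24.

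| Dropout, supervised v control | Completer ANCOVA | Imputed from arm and baseline | Week 12 added, r = 0.5 | Week 12 added, r = 0.7 |
|---|---|---|---|---|
| 15% v 15% | 0.00 / 0.00 | 0.00 / 0.00 | 0.00 / 0.00 | 0.00 / 0.00 |
| 20% v 10% | 0.06 / 0.09 | 0.06 / 0.09 | 0.06 / 0.08 | 0.04 / 0.06 |
| 25% v 5% | 0.13 / 0.19 | 0.13 / 0.19 | 0.11 / 0.17 | 0.08 / 0.13 |
| 10% v 20% | −0.06 / −0.10 | −0.06 / −0.10 | as row 2, sign reversed | as row 2, sign reversed |

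Against the planned 0.5 SD, the completer bias is 0.06/0.5 = 12% to 0.19/0.5 = 38%.

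**Other mechanisms.**
- Dropout completely at random, or dependent only on baseline: completer bias about 0.00 at every split tried.
- Dropout dependent on week-12 status, 25% v 5%, week 12 to week 24 correlation 0.5: completer bias 0.04 (slope 1) or 0.06 (slope 2). Imputation that includes week 12 brings both to about 0.00.

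**Which outcomes have a week-12 value.** Assessment protocol limits the midpoint to patient-reported outcomes, and the abstract agrees; Design is worded more loosely. If Assessment protocol governs, the squat, jump and isometric tests have no midpoint value of their own to impute from.

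**The case against.** The strongest objection is that changing the primary set gains little against the bias just quantified. That bias arises when dropout follows the unseen week-24 outcome, whereas MICE assumes data missing at random. In the table, imputation from baseline removes none of it, and adding week 12 removes roughly a tenth to a third. When dropout depends only on baseline, the completer ANCOVA is already about unbiased. This stands. The clear gain from the swap is for questionnaires, when week-12 scores predict who leaves. A reader might infer that promoting the planned MICE analysis cures the problem; it does not on its own.

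A reader might also infer that the design favours supervised training. The documents do not support that. They give one dropout rate for both arms, and Program monitoring and safety lists transport help, flexible scheduling and follow-up calls, which could lower loss in the supervised arm. If the home arm loses more men, the sign reverses and a real benefit could be hidden.

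Nor does the article say that a withdrawn man goes untested at week 24. The primary set turns on completing assessments, not on finishing the exercise, so a man who stops training but is tested stays in. His loss is an inference from silence, and a condensed article may leave that detail to the full protocol.

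Finally, the intention-to-treat result will be reported anyway, and the simulated bias is below one standard error: √(1 − 0.5²) × √(4/44) = 0.26 SD at N = 44. Both are true and keep the concern in proportion. But a confidence interval does not allow for bias, and the stated primary analysis is the one that carries the conclusion.

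**Conclusion.** The concern holds as a matter of exposure to bias, not of demonstrated bias. The article itself fixes the completer set as primary and offers no justification, so this is not a detail left to an unseen analysis plan. About 15% of randomised men would be outside the main result. Bias of 0.06 to 0.19 SD in either direction rests on three assumptions: dropout differs between arms (20% v 10% to 25% v 5%), it is related to the week-24 outcome with the slopes given, and the baseline correlation is 0.5. Without unequal, outcome-related loss the bias is about zero. The per-protocol set, "Per-protocol analyses will be conducted as sensitivity analyses, including only participants with ≥ 85% adherence", is a sensitivity analysis, cannot bias the main result, and is no part of this point.

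**What to change.** 1. In Statistical analyses, make the primary analysis all randomised participants in their allocated arm, using the planned ANCOVA with MICE. For patient-reported outcomes, put week-12 scores in the imputation model, or use a mixed model on baseline, week 12 and week 24. Make the completer analysis a sensitivity analysis.
2. In Program monitoring and safety, state that stopping the exercise programme, or being withdrawn from it, does not end follow-up, and that week-24 assessments are still sought, at least the electronic questionnaires. This concerns data collection only and leaves the clinical grounds for withdrawal as they are. It matters most for the physical tests, where imputation has least to work with.
3. Add a delta-adjusted missing-not-at-random sensitivity analysis that shifts imputed week-24 values over a prespecified range, separately by arm.

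The cost is a paragraph of wording, an amendment by the route the Design section already describes, and modest effort to reach men who have stopped exercising. ANCOVA and MICE are already planned, and the target of 52 does not change. The change should be made before outcome data are analysed, so that it cannot look driven by the results.
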